## Abstract

**Background:**

Poor mental health and adverse childhood experiences (ACEs) predict extensive adverse outcomes in youth, including increases in long-term risk for chronic disease and injury, impaired emotional development, and poor academic outcomes. Exposure to school violence, specifically intentional gun violence, is an increasingly prevalent ACE. The anticipation of school shootings has led to the implementation of school safety and security interventions that may increase anxiety, depression, and other indicators of poor mental well-being among students and staff alike. Despite this, the association between exposure to existing school safety interventions and early adolescent student mental health outcomes, while accounting for one's history of ACEs, has not been previously investigated.

**Objective:**

The study protocol described here aims to determine whether there is a significant difference in the prevalence of mental health outcomes, perceived school safety, and academic engagement between adolescent students (grades 6-12) at schools who have experienced a school shooting and those who have not; whether existing interventions to promote school safety and security are associated with poor mental health outcomes among students and school staff; and what the strength of the association between school safety interventions and mental health outcomes among students and teachers is in schools that have experienced a school shooting versus schools that have never experienced a school shooting.

**Methods:**

This observational study will collect cross-sectional survey data from a nationwide sample of students, teachers, and principals at 12 secondary public schools across the United States. The participants come from 6 randomly selected exposure schools that have either experienced a recent (<2 years ago) intentional school shooting or have experienced an intentional school shooting less recently (>2 years ago). Data from these schools are being directly compared with 6 secondary schools that have never experienced a school shooting.

**Results:**

Institutional review board approval for this research project was obtained and the study subsequently began its recruitment and data collection phase in January 2024. Data collection is currently ongoing and the expected completion date is January 2025. The analytic plan is designed to determine if the strength of the association between school safety interventions and mental health outcomes differs among students and school staff in schools with varying levels of school violence exposure. Analyses will be used to evaluate the role of ACEs on the relationships among exposure to an intentional school shooting, exposure to school safety strategies, and student outcomes (ie, mental health and well-being, perceptions of school safety, and educational outcomes).

**Conclusions:**

The results from this study promise to generate meaningful and novel findings on the extent to which having a prior history of ACEs moderates the relationships among exposure to intentional school gun violence, school safety strategies, and student outcomes (ie, mental health and well-being, and perceptions of school safety).

**Trial Registration:**

ClinicalTrials.gov NCT06153316; https://clinicaltrials.gov/study/NCT06153316

**International Registered Report Identifier (IRRID):**

DERR1-10.2196/56249

## Introduction

### Background

Poor mental health and the prevalence of adverse childhood experiences (ACEs) have substantially increased among the youth in the United States over the past decade. This increase has been confirmed through independent national surveys, hospital admissions related to self-harm, and death by suicide, which has tripled for girls and doubled for boys aged 10-14 years [1-5]. Moreover, recent data from the Adolescent Behaviors and Experiences Survey conducted by the Centers for Disease Control and Prevention and others [6] have underscored that indicators of poor mental health among adolescent youth have persisted during the COVID-19 pandemic [7]. These increases have occurred concomitant with substantial increases in school shootings across the United States [8,9].

Exposure to gun violence over the past several years has catalyzed a national movement that has sought to increase school gun violence preparedness and safety. K-12 (the grades of kindergarten and 1st-12th grade) schools that have experienced intentional gun violence have implemented a number of policies specifying tactics designed to keep their schools safe and secure from future acts of violence. These have included arming teachers with firearms, using metal detectors, and implementing “zero tolerance” discipline policies [10-14]. Nearly all public schools that have not experienced intentional gun violence have responded to the anticipation of such incidents by implementing some form of school safety and security measures; as of 2019, 96% of all K-12 public schools in the United States reportedly conduct lockdown drills [15].

Although the pursuit of these efforts has value, research suggests that some of these interventions may not be beneficial and may decrease student perceptions of safety in their schools [10-12]. Additional research has drawn connections between perceived school safety and self-reported mental health symptoms among the youth [16]. However, little research has documented the burden of mental health problems on cohorts of students subsequent to actual as well as anticipated school gun violence. Understanding the nature and scope of this burden is critical for designing effective school safety interventions that attend to youth mental health needs while also accounting for prior histories of ACEs among students. In addition, there is scant research evaluating the mental health needs and perceptions of safety among school staff who have been present during a school shooting or who are also exposed to school safety interventions, or both.

### Mental Health and Gun Violence

Poor mental health symptoms among youth predict extensive co-occurring adverse outcomes, including increases in long-term risk for chronic disease and injury, impaired child development, and poor academic outcomes [17-21]. This observed increase in prevalence of mental health problems followed the 2012 Sandy Hook Elementary School shooting, and perhaps not by coincidence—since January 2012, there have been hundreds of incidents of intentional gun violence on school grounds [8,9]. Thousands of children have been exposed to gun violence, specifically in school, during this same period [22]. Indeed, children are now often referred to as being a part of the “mass shooting generation,” a cohort of youth growing up in the presence of gun violence [23].

The prominence of gun violence in communities across the United States is likely and, unsurprisingly, has a substantial impact on the mental well-being of adults, with over 40% of US adult residents expecting that they or an immediate family member could become a victim of gun violence [24-28]. In particular, school staff must now contend with gun violence or the possibility of gun violence in their schools. This burden also requires them to attend to the mental health needs of their students, and for some educators, reckoning with exposure to gun violence or the possibility of such exposure may take a significant emotional and physical toll. The National Education Association has referred to this phenomenon as “secondary traumatic stress” [29]; however, there is need for research that more clearly establishes the strength of the relationships among students and school staff who have either been exposed to gun violence or are contending with the anticipation of gun violence, and their mental health and well-being.

### Adverse Childhood Experiences

The scientific literature conceptualizes ACEs as stressful or traumatic events that exert harmful impacts on the healthy development of children through adolescence and into adulthood [30]. Although historically research on ACEs has focused on child abuse and maltreatment, ACEs are now understood to include a wider range of traumatic events, including youth experiences with the juvenile justice system, household mental illness, family members who have been incarcerated, and childhood exposure to gun violence [17,18,30-33]. The cumulative and long-term influence of ACEs on multiple harmful and injurious behaviors has been well established [18]. Research has confirmed that ACEs increase a person’s risk of poor mental health, illicit drug use, self-harm behaviors, and premature mortality [18,19]. The impact of the toxic stress typically associated with ACEs on a child’s brain development is also well-documented [20]. More recently, research has established a clear relationship between an increased number of ACEs and poor academic outcomes in children [17]. Thus, it is quite possible that those students who have a higher number of ACEs may experience poorer mental health and educational outcomes following exposure to intentional school shootings and school safety strategies implemented in response to the anticipation of such violence, in comparison with their peers who have experienced very few or any ACEs. At the same time, there is an emerging body of research on positive childhood experiences (PCEs), which include feeling a sense of belonging, having meaningful and positive relationships, and that collectively may mitigate the impacts of ACEs on child outcomes [34]. This work will seek to understand and incorporate the role of PCEs on youth mental health, well-being, perceived safety, and learning.

### Exposure to School Violence

Previous research has shown that exposure to different forms of violence are ACEs in and of themselves [32,33]. Similar to other ACEs, the impact of exposure to violence on children’s short- and long-term health outcomes is significant. For example, research has demonstrated that children and adolescents who have recently witnessed violence are more likely to experience symptoms of trauma, including the onset of posttraumatic stress [15,35]. There are multiple studies confirming that exposure to violence during childhood is associated with poor chronic health outcomes and poor mental health, as well as a significant increase in the likelihood that young people who are exposed to violence will perpetrate violent crime themselves [33,36-38]. Moreover, there is a substantial body of research on school violence that has linked youth exposure to violence, specifically in school settings with multiple poor health and learning outcomes, such as decreased motivation to learn and lower classroom engagement [17,39]. Not surprisingly, exposure to violence also influences health outcomes during adulthood (including increasing one’s likelihood for depression and other poor mental health outcomes, sleep quality, chronic disease, and substance use) [30,40-42]. The effect of exposure specifically to intentional school gun violence on youth and adult mental health outcomes and youth educational outcomes, however, has not been comprehensively documented.

### Influence of School Climate

A robust set of research confirms that children who feel dissatisfied with, disconnected from, or unsafe within their school environment are more likely to experience poor health and learning outcomes [39,43-45]. If young people feel unsafe or threatened, their ability to focus and perform academically is drastically reduced [39]. Furthermore, perceptions of safety at school and prior exposure to violence have been, and continue to be, highly correlated with engagement in many risk behaviors [43-45]. Conversely, a nurturing school climate that fosters cohesion and student satisfaction with their academic learning has been shown to offset high-risk behaviors [45]. However, there has been an uptick in intentional school gun violence over the past few years [8,9]. In addition to likely influencing a school’s social and emotional climate [46], exposure to such violence has substantial implications for a school’s physical environment and has prompted schools, both those that have experienced intentional gun violence and those that have not, to increase school violence preparedness [10-15]. Such school safety tactics include target hardening efforts, zero-tolerance policies, presence of armed school resource officers and armed teachers, and emergency preparedness programs [10-14,47-49]. While there are a number of strategies available to schools, there is very limited empirical evidence as to their effectiveness. Of the evidence that exists, certain security efforts have been shown to be ineffective at deterring violence and may even have a criminalizing effect on a school’s climate [10,12]. Given this collective body of work, it is reasonable to hypothesize that these school safety strategies may contribute to poor mental health and distress among students and staff. There is, however, very limited empirical work that has evaluated this relationship [29,50].

### Purpose

Poor mental health symptoms and ACEs among the youth predict extensive co-occurring adverse outcomes, including increases in long-term risk for chronic disease and injury, impaired child development, and poor academic outcomes [17-20]. At the same time, the anticipation of school shootings has fueled school safety and security interventions that may inadvertently increase anxiety, depression, and other indicators of poor mental well-being among students and staff alike [29,50]. Despite this, the association between exposure to existing school safety interventions and student mental health outcomes, particularly beginning in early adolescence, is not clear. It is also unclear whether, how, and to what extent the strength of these associations might differ among students and staff members from those schools that have more recently experienced a school shooting, those that have experienced a school shooting less recently, and those that have never directly experienced a school shooting but are nonetheless indirectly aware of these tragic events via media and other networks. Finally, we do not know whether and to what extent having a prior history of ACEs moderates the relationships among exposure to school shootings, exposure to school safety strategies, and student outcomes (eg, perceptions of school safety and academic achievement). The role of PCEs is also unknown. This study therefore seeks to fill these critical research gaps by answering the following questions:

Is there a significant difference in the prevalence of mental health outcomes, perceived school safety, and academic engagement between early adolescent and adolescent students (grades 6-12) at public secondary schools that have experienced a school shooting and those that have not?Are existing interventions to promote school safety and security associated with poor mental health outcomes among students and school staff members?Does the strength of this association between school safety interventions and mental health outcomes differ among students and teachers who have experienced an intentional school shooting versus students and teachers who never experienced a school shooting? Furthermore, are these associations moderated by student ACE history?

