#### Exposure School Selection

Our research team is identifying all possible intentional school shooting cases via a comprehensive review of multiple national school shooting databases, including the K-12 School Shooting database, the Everytown for Gun Safety database on gunfire on school grounds, and the Washington Post database on school shootings, to identify all schools that have experienced intentional gunfire on campus during school hours [51]. These data document all incidents in which a gun is fired or a bullet hits school property for any reason, regardless of the number of victims, time, or day of the week. Our research team is then coding this list of incidents to identify cases that meet the criteria for intentional school shooting at a secondary (ie, middle or high school level) public school—all cases of intentional gunfire on school property, occurring during school hours (including 1 hour before official school activities begin and 1 hour after all official school activities end), beginning January 1, 2015—to ensure we have enough schools in our sampling frame that meet our aforementioned criteria. We are excluding accidental discharges and attempted suicides where no other person was targeted or shot. We are also excluding any incidents taking place on a school bus and on school property that are noncontiguous with the school’s primary campus. Furthermore, we are cross-referencing our list of incidents with other publicly available data sources [40] to ensure that no incidents meeting our criteria are missed. Two members of our research team are then independently coding this list of incidents to identify the cases that meet our proposed study’s criteria for “intentional school shooting”; a third member of our study team is reviewing any potential discrepancies in coding efforts. The final list of exposure schools will then be divided into 2 based on recentness, that is, schools where the incident happened between January 1, 2015, and December 31, 2021, and schools where the incident happened between January 1, 2022, to December 31, 2023. In total, 3 schools will be randomly selected from each list. In case a school declines to participate, we will move to the next randomly selected school. Nonexposure schools will be matched to the final exposure schools. In case a school declines to participate, we will move to the next randomly selected school.

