#### Students

Within each participating school, all students between grades 6 to 12 are eligible for and invited to participate in this study. To encourage study participation, we are implementing reasonable incentives for participants, keeping the survey as brief as possible, communicating study expectations clearly and consistently, engaging thoughtfully with each school’s leadership team during the recruitment process, and using other best practices [56,57]. Accounting for attrition and individuals choosing not to participate, we expect a 15% to 20% response rate (which is consistent with other research that has involved collecting survey data directly from students, teachers, and principals) [58,59], and therefore, anticipate sampling between 1000 to 1200 students across the 12 participating schools.

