#### Demographics

Data on sex, race, age, grade-level, and presence or not at the time of the school shooting incident for students in the exposure school will be provided by each student at the beginning of the survey. Self-report data on teacher and principal demographics (eg, their length of time working at the school) will also be collected at the beginning of the teacher and principal surveys, respectively.

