### Data Analysis Plan

The data collected from the students, teachers, and principals across all 12 participating schools will be analyzed and will fully respond to each of the research questions. Descriptive statistics will be calculated to summarize student and teacher participant characteristics within each school and also describe each school’s safety and security strategies. Analyses of covariance will subsequently be used to identify potential significant differences in the prevalence of mental health and well-being, perceptions of school safety, educational outcomes, and ACEs among students in schools that have more recently experienced an intentional school shooting, schools that have experienced an intentional school shooting less recently, and schools that have never experienced a shooting, while controlling for key covariates.

ANOVA will also be used to identify potential significant differences in the prevalence of mental health and perceptions of school safety among teachers in schools that have more recently experienced an intentional school shooting, schools that have experienced an intentional school shooting less recently, and schools that have never experienced an intentional school shooting. We used G^*^Power (version 3.1; Heinrich Heine University Düsseldorf) to run power analyses in anticipation of our proposed analyses, assuming an α level of .05 and a power of 0.80. In the case of our proposed student analyses, a very small minimum effect size will need to be detected to meet our power requirements and given our anticipated minimum sample size (exposure schools: N=500-600, nonexposure schools: N=500-600). In the case of our teacher analyses, a medium effect size will need to be detected and given our anticipated minimum sample size (exposure schools: N=30-60, nonexposure schools: N=30-60). On the basis of the average enrollment across secondary public schools in the United States, we should be able to reach the minimum sample size from 12 schools.

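### Question 3 asks about people who experienced a shooting, but exposure is assigned by school, so recent versus less-recent differences among students may reflect cohort turnover

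*Protocol article*

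**What the plan says.** In Purpose, question 3 asks whether the association between safety interventions and mental health outcomes would "differ among students and teachers who have experienced an intentional school shooting versus students and teachers who never experienced a school shooting". The abstract's Objective words the same aim by school: "in schools that have experienced a school shooting versus schools that have never experienced a school shooting".

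Exposure School Selection forms two lists by incident date. The less-recent list holds "schools where the incident happened between January 1, 2015, and December 31, 2021"; the recent list holds "schools where the incident happened between January 1, 2022, to December 31, 2023". From these, "3 schools will be randomly selected from each list". Within a school, "all students between grades 6 to 12 are eligible for and invited to participate in this study" (Students, under Sampling Frame), with no condition on when a student joined.

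In the Data Analysis Plan, the covariance analyses look for differences "among students in schools that have more recently experienced an intentional school shooting, schools that have experienced an intentional school shooting less recently" and never-exposed schools. The later regressions also group students and staff by their school's degree of exposure.

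Demographics records that "presence or not at the time of the school shooting incident for students in the exposure school will be provided by each student". Neither the Data Analysis Plan nor the list in Independent Covariates mentions this item. For teachers, time worked at the school is collected, but no presence item is named.

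Recentness gives two reasons for the cutoff. One is to tell an early from a later effect on young people's mental health, argued from the onset of posttraumatic symptoms. The other is to compare schools still in upheaval with schools that have had time to adapt.

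**The concern.** A current student at a school with an incident in, say, 2017 attends a school with a history but did not live through the event there. If exposure is assigned by school and all current students are surveyed, the share who were there falls as the incident recedes. Recency and share present then move together.

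Two things are at stake. Question 3, read as worded, is not answered by the groupings described. And a smaller difference in less-recent schools could be taken as fading of the effect when it may only show that the affected students have left.

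**Working it through.** **Stated figures.** The article gives no share of students present, so there is none to reproduce. It describes the detectable student effect only in words, as very small. With 500–600 students per arm, two-sided α .05 and power .80, the two-group value is d = 0.16–0.18. That fits the wording, but it applies to the contrast by school status.

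**Inputs from the article.** Less-recent incidents: 1 January 2015 to 31 December 2021. Recent incidents: 1 January 2022 to 31 December 2023 (Exposure School Selection). Surveys: January 2024 to January 2025 (Results). Students at exposure schools: 500–600 (Data Analysis Plan).

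**Assumptions.** High schools have 4 grades and middle schools 3 (spans are not stated). Grades are of equal size, nobody transfers or repeats, the school year runs August to May, and incidents are spread evenly over school months.

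**Formula.** Share enrolled at the incident = max(0, G − gap)/G, where G is the number of grades and gap is the number of school years between incident and survey. Within a school this is an upper bound on presence, since an enrolled student may have been absent that day.

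| Incident school year | Less-recent months | Recent months | High, spring 2024 | Middle, spring 2024 | High, autumn 2024 on | Middle, autumn 2024 on |
|---|---|---|---|---|---|---|
| 2019/20 or earlier | 55 | 0 | 0 | 0 | 0 | 0 |
| 2020/21 | 10 | 0 | 25% | 0 | 0 | 0 |
| 2021/22 | 5 | 5 | 50% | 33% | 25% | 0 |
| 2022/23 | 0 | 10 | 75% | 67% | 50% | 33% |
| 2023/24 | 0 | 5 | 100% | 100% | 75% | 67% |

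**Less-recent group (70 months).**
- High, spring: (10×0.25 + 5×0.50)/70 = 7.1%. Autumn: 5×0.25/70 = 1.8%.
- Middle, spring: 5×0.333/70 = 2.4%. Autumn: 0%.
- Months for which no current student was enrolled: high 55/70 = 79% (spring) and 65/70 = 93% (autumn); middle 65/70 = 93% and 100%.

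**Recent group (20 months).**
- High, spring: (5×0.50 + 10×0.75 + 5×1)/20 = 75%. Autumn: (5×0.25 + 10×0.50 + 5×0.75)/20 = 50%.
- Middle, spring: (5×0.333 + 10×0.667 + 5×1)/20 = 67%. Autumn: (10×0.333 + 5×0.667)/20 = 33%.

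**Sensitivity.** Weighting incidents towards later years raises the less-recent shares to 9–16% (spring) or 2–5% (autumn) for high schools, and 3–6% or 0% for middle schools. A school spanning grades 6–12 averages 25% (spring) or 16% (autumn), against 85% and 71% in the recent group. The highest single-school values, for an incident in autumn 2021, are 50% (high) and 33% (middle) in spring 2024.

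**Head count.** Three of six exposure schools, taken as equal in size, give about 250 of 500 students. The expected number enrolled at the incident is between 0 and 250×0.071 ≈ 18. One high school with an autumn 2021 incident would alone contribute 250/3×0.5 ≈ 42 in spring 2024.

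**Effect of turnover alone.** Suppose the effect on those present is a constant δ that never fades, and is zero for everyone else. In high schools surveyed in spring 2024, the expected group effects are 0.75δ (recent) and 0.07δ (less recent). The gap of 0.68δ is all turnover. From autumn 2024 it is 0.50δ − 0.02δ = 0.48δ.

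**Detectability.** For 250 less-recent against 500 nonexposed students, treated as independent, d ≈ 2.80×√(1/250 + 1/500) = 0.22. If only 5–10% were present and only they are affected, the effect in them would have to be 0.22/0.10 ≈ 2.2 to 0.22/0.05 ≈ 4.4.

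**The case against.** The best defence is that the study is about schools almost throughout. The abstract's Objective, the text leading into the questions, the sampling and the analyses all group by school, so question 3 may be shorthand for that contrast. This stands as far as it goes. The school contrast is legitimate for question 1, for the aim as the abstract words it, and for comparing schools in upheaval with schools that have adapted. It does not rescue the claim in Recentness about early versus later effects on young people's mental health, which concerns those who lived through the event.

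Second, the article is a condensed account. The covariates in the covariance analyses are not listed, and a fuller plan may use the presence item. So one may say only that no described analysis names it. A reader might infer that it goes unused, and the documents do not show that. Even as a covariate, though, presence would not define the contrast in question 3.

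Third, person-level exposure does enter through the adverse childhood experiences score, which includes gun violence and violence in school. But that is a sum score and cannot isolate the index incident.

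Fourth, the turnover argument covers students only. Teachers need not leave in 3 or 4 years, and their time at the school is collected.

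**Conclusion.** The concern holds in limited form. Question 3 is worded for people, the exposure groupings described are by school, and no described analysis names presence. Among students, recency is expected to be strongly confounded with the share enrolled at the time: about 2–7% against 50–75% in high schools, and 0–2% against 33–67% in middle schools.

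A reader might go further and infer that almost no less-recent student was there. The documents do not support that as fact. The shares are averages under assumed grade spans and evenly spread incidents, and the dates for the three schools drawn are not given. An incident in December 2021 and one in January 2022 fall in the same school year and give the same share. The ordering of the averages survives the later-weighted runs and the 6–12 case, but the size of the gap in the actual sample has to be observed.

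Nor does it follow that the school comparison is invalid, or that teachers in less-recent schools were absent.

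**What to change.** - Keep the school contrast for question 1 and for the aim as the abstract words it.
- For question 3, prespecify a student analysis in three groups: present at the incident, at an exposure school but not present, and at a nonexposure school. Adjust for grade or age. Under the no-transfer assumption, those enrolled at an autumn 2021 incident are all in grades 11 and 12 of a high school surveyed in spring 2024, so presence is tied to grade within a school.
- For teachers, derive presence by setting time at the school against the incident date.
- Report the share present for each exposure school.
- Do not read recent versus less recent among students as immediate versus longer-term impact without the split by presence, and qualify the Recentness section accordingly.
- If the person-level analysis is not adopted, reword question 3 as a contrast between schools.

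The cost is analysis and wording only, because the student item and teacher tenure are already collected. The present group in less-recent schools may be small enough to be descriptive only. The article's power statement does not carry over to the person-level contrast and would have to be redone for it.
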